# Treatment of neonatal jaundice with filtered sunlight in Nigerian neonates: study protocol of a non-inferiority, randomized controlled trial

**DOI:** 10.1186/1745-6215-14-446

**Published:** 2013-12-28

**Keywords:** Filtered sunlight phototherapy, Hyperbilirubinemia, Developing country, Low-cost technologies, Irradiance, Africa

## Abstract

**Background:**

Severe neonatal jaundice and its progression to kernicterus is a leading cause of death and disability among newborns in poorly-resourced countries, particularly in sub-Saharan Africa. The standard treatment for jaundice using conventional phototherapy (CPT) with electric artificial blue light sources is often hampered by the lack of (functional) CPT devices due either to financial constraints or erratic electrical power. In an attempt to make phototherapy (PT) more readily available for the treatment of pathologic jaundice in underserved tropical regions, we set out to test the hypothesis that filtered sunlight phototherapy (FS-PT), in which potentially harmful ultraviolet and infrared rays are appropriately screened, will be as efficacious as CPT.

**Methods/design:**

This prospective, non-blinded randomized controlled non-inferiority trial seeks to enroll infants with elevated total serum/plasma bilirubin (TSB, defined as 3 mg/dl below the level recommended by the American Academy of Pediatrics for high-risk infants requiring PT) who will be randomly and equally assigned to receive FS-PT or CPT for a total of 616 days at an inner-city maternity hospital in Lagos, Nigeria. Two FS-PT canopies with pre-tested films will be used. One canopy with a film that transmits roughly 33% blue light (wavelength range: 400 to 520 nm) will be used during sunny periods of a day. Another canopy with a film that transmits about 79% blue light will be used during overcast periods of the day. The infants will be moved from one canopy to the other as needed during the day with the goal of keeping the blue light irradiance level above 8 μW/cm^2^/nm.

Primary outcome*:* FS-PT will be as efficacious as CPT in reducing the rate of rise in bilirubin levels. Secondary outcome: The number of infants requiring exchange transfusion under FS-PT will not be more than those under CPT.

**Conclusion:**

This novel study offers the prospect of an effective treatment for infants at risk of severe neonatal jaundice and avoidable exchange transfusion in poorly-resourced settings without access to (reliable) CPT in the tropics.

**Trial registration:**

ClinicalTrials.gov Identifier:
NCT01434810

## Background

Severe neonatal jaundice (NNJ) or hyperbilirubinemia and its progression to acute bilirubin encephalopathy (ABE) and kernicterus is a leading, yet preventable, cause of newborn re-hospitalizations, deaths, and disabilities globally
[1-5]. Phototherapy (PT), which involves exposing a newborn’s skin to electric lamp-generated blue light, is the standard treatment for removing excessive bilirubin, except in extreme cases when exchange transfusion becomes necessary
[6].

Numerous studies from poorly-resourced countries suggest that severe NNJ represents perhaps the largest unrecognized cause of neonatal morbidity and mortality in the world
[4,7]. In sub-Saharan Africa, especially in Nigeria and Kenya, NNJ is a leading cause of death in newborn nurseries
[8-13] and long-term neurological impairment in survivors
[14-18]. Unfortunately, PT may not be available in these countries because of the lack of devices and/or of reliable electrical power
[19,20]. In these areas, modern PT devices are not readily affordable, often break down because of electrical power surges, and are difficult to maintain due to the unavailability of replacement parts. Even where PT devices are available, most hospitals lack the resources necessary to replace fluorescent lamps, which is recommended after 2,000 to 3,000 hours of use, and, as a consequence, simply leave ineffective tubes in place until they burn out. Moreover, very few hospitals have appropriate irradiance meters for measuring the intensity of the blue light emitted by the lamps, resulting in few or no devices providing the optimal level of irradiance required for intensive (>30 μW/cm^2^/nm) conventional phototherapy (CPT)
[21,22]. However, it is not uncommon, especially in areas without access to CPT, for the parents/guardians of jaundiced infants to place their babies in direct sunlight unaware of the potential harm or safety risks.

The scientific potential of sunlight as a possible treatment for NNJ was first demonstrated by Cremer and colleagues in 1958
[23]. His team found that placing naked infants in sunlight decreased bilirubin levels. This observation led to the production of the first PT device using fluorescent blue light tubes. These early studies subsequently led to the development of commercially available, easily controlled, electricity-requiring artificial blue light sources for effective, on-demand PT of newborns in industrialized countries. The potential efficacy of direct sunlight PT compared with CPT has also been demonstrated in an *in vitro* study
[24].

Using direct sunlight for PT has a number of clinical and practical drawbacks that could make its use undesirable. Sunlight contains altitude-, seasonal-, and time-of-day-dependent levels of harmful ultraviolet A, B, and C radiation, which can seriously and permanently damage human skin. It also contains significant levels of warming infrared radiation, which, in the absence of sufficient cooling, could raise core body temperatures to unsafe levels. However, several technological solutions exist for filtering unwanted radiation from any light source, including sunlight, while preserving the desirable attributes of a given energy spectrum
[25]. When filtered to exclude the harmful spectral radiation, the use of sunlight can be valuable in environments that have no access to electric lamp PT.

The most practical filters of sunlight are the commercially available window-tinting films, widely used in vehicles and residential and commercial structures in sunny climates. Although window-tinting films are traditionally affixed to a glass surface, these films can also be stretched over a support frame, under which an infant basket (Figure 
1A), bassinet, or crib (Figure 
1B) can be placed. Our preliminary laboratory bench studies in California and field studies in Nigeria have shown that such films effectively remove potentially harmful radiation, while allowing the transmission of beneficial blue light required for effective PT. The levels of irradiance recorded exceeded that delivered by the most potent newborn PT devices. In one of the field tests in a rural hospital in Nigeria, seven jaundiced infants were placed under portable individual or group filtered sunlight PT (FS-PT) using film-covered canopies placed in direct sunlight in the hospital courtyard (Figure 
1B,C). Body temperature and blue light irradiance were monitored every hour, and the infants were watched closely for the development of clinical dehydration and sunburn. FS-PT was tolerated well by both newborns and their mothers and allowed for maternal bonding during treatment. None of the infants developed significant hypothermia (defined as <35.5°C), and displayed no evidence of dehydration or sunburn. Six of the infants had at least one temperature episode >38.0°C during their course of FS-PT, but none exceeded 39°C, and all recovered after being returned indoors. The average time to being able to return to FS-PT was 19.7 minutes, with only two instances over 60 minutes. Moreover, placing infants on a moistened towel during high ambient temperatures (>40°C) quite readily maintained body temperatures of infants in cribs.

**Figure 1 F1:**
[figure not shown]
**Filtered sunlight canopies. A**: Experimental filtered sunlight canopy with a baby doll; **B**: Baby placed under a filtered sunlight canopy in an open lawn in a primary care setting; **C**: Mother-infant pairs with health workers under a group filtered sunlight canopy in a hospital setting.

### Observational study on the safety and potential efficacy of filtered sunlight phototherapy

A recent comprehensive systematic review of available evidence worldwide on PT found no randomized controlled trials (RCTs) dealing with either sunlight or environmental light
[26]. Prior to our proposed RCT to establish the effectiveness of FS-PT compared with CPT in a larger sample of infants, we conducted an observational study to evaluate safety and potential efficacy of two previously tested films for use in an inner-city maternity hospital in Lagos, Nigeria. FS-PT safety was determined through close monitoring of infant temperature, hydration status, and skin for signs of possible sunburn. Therapy was deemed safe on a given day if the infant did not have to be removed from phototherapy due to needing physician treatment for sunburn or dehydration, due to persistent temperature instability defined as two or more episodes of temperatures <35.0 or >39.0°C, or due to failure to return to normothermia (defined as 35.5 to 38.0°C) within 1 hour of being removed from FS-PT. Efficacy was evaluated by measuring the rate of rise/decline in total serum/plasma bilirubin (TSB) levels. Treatment was deemed safe and efficacious if the infant was able to stay in the FS-PT canopy for ≥5 hours per day and the rate of rise of TSB was <0.2 mg/dl/hour for infants ≤72 hours of age or if TSB decreased for infants >72 hours of age. This study was concluded in August 2012, details of which are scheduled for publication shortly. In summary, 203 term and near-term newborns (≤14 days old) with clinically significant jaundice as assessed by TSB levels were enrolled. They received treatment under a FS-PT canopy over a period of 227 days. Hourly measurements of axillary body temperatures and monitoring of sunburn, dehydration, and irradiances of FS-PT were performed. The results showed that FS-PT was efficacious in 94% (164/175) of the infants studied. Average irradiance from FS-PT was 37 ± 14 (range 8 to 65) μW/cm^2^/nm as measured by the Bili-Blanket Meter II^©^ (General Electric, Fairfield, CT, USA). No infant developed sunburn or dehydration, nor met exclusion criteria. Based on these favorable findings with our selected films (Gila Titanium and Air Blue 80 produced by CP Films Inc. Subsidiary of Eastman Chemical Co. Fieldale, VA, USA), we set out under the second phase of this project to demonstrate primarily in a RCT that FS-PT is just as efficacious as CPT in the treatment of infants with or at risk of severe NNJ.

## Methods/design

### Aims and hypotheses

The primary goal of this study is to demonstrate that the efficacy of FS-PT is no worse than that of CPT, with a non-inferiority margin of 10%. In effect, our null hypothesis is that this margin is above 10% suggesting that FS-PT is inferior to CPT.

The secondary goal of the study is to demonstrate that the proportion of infants who require exchange transfusion under FS-PT is no worse than that under CPT, with a non-inferiority margin of 5% based on a clinical rationale that FS-PT is non-inferior to CPT and still better than no treatment. This was also informed by the results of a meta-analysis of RCTs comparing CPT with no treatment which estimated that 10 infants needed to be treated with CPT to prevent an exchange transfusion
[26].

### Study design

This is a prospective, non-blinded, single center, randomized two-stage controlled non-inferiority clinical trial. During the first stage of the study, infants will be referred from elevated transcutaneous bilirubin (TcB) screening and enrolled for the definitive TSB estimation. Only infants with significantly elevated TSB levels will qualify for inclusion into the second stage of the study for PT treatment and will be randomly assigned to receive FS-PT or CPT.

### Study setting

The study location is Island Maternity Hospital (IMH), Lagos, Nigeria, which is a state-owned hospital. It has a special care baby unit with CPT and other basic neonatal care facilities, including intravenous (IV) fluids, antibiotics, and exchange transfusion. Ventilator support and pumps for giving IV fluids are not available. It is a 180-bed residency teaching hospital with about 300 deliveries per month of which 45 infants (15%) would be expected to qualify for PT. It is possible at this location to give routine care, IV fluids, antibiotics, oxygen, and medications without interrupting PT. The average maximum temperature in Lagos is 32°C (90°F) during the dry season (November to March), with a maximum recorded temperature of 40°C (104°F), making FS-PT possible even with infants unclothed or minimally clothed. In the rainy season it should be possible to maintain satisfactory irradiances in the absence of an excessively overcast sky. This site was chosen for the maiden study to ensure that back-up neonatal care services are readily available when required until we have the required safety and efficacy data.

### Definition of high-risk threshold

All jaundiced infants with elevated TSB, defined as 3 mg/dl below the level recommended by the American Academy of Pediatrics (AAP)
[27] for PT in high-risk infants, will be considered at high risk. The high-risk classification category of the AAP guideline was selected because laboratory evaluation for hemolysis will not be consistently available during the study, and Nigerian infants are known to be at higher risk for severe NNJ secondary to glucose-6-phosphate dehydrogenase (G6PD) deficiency
[28]. This TSB level was chosen also because many hospitals begin PT about 2 to 3 mg/dl below the current level in the United States, due to the severity of NNJ and the sub-optimal PT treatment in most locations in Nigeria.

### Primary outcome

The primary outcome for the RCT is efficacy of FS-PT compared with CPT.

#### Evaluation criteria

Change in TSB level per hour of therapy defined as a binary variable. The TSB level will be measured immediately before beginning therapy on a given day and immediately after therapy is completed that day, and the change in bilirubin level in mg/dl per hour of therapy will be calculated. For infants who are less than 72 hours old in the morning, the treatment will be judged efficacious if the bilirubin level rises more slowly than 0.2 mg/dl per hour of therapy that day. For infants who are more than 72 hours old, the treatment will be judged efficacious if the bilirubin level falls. Efficacy will be evaluated only for days in which the treatment was deemed safe (that is, when the infant did not have to be removed from PT due to a need for physician treatment for sunburn or dehydration, persistent temperature instability defined as two or more episodes of temperatures <35.0 or >39.0°C, or failure to return to normothermia (defined as 35.5 to 38.0°C) within 1 hour of being removed from PT). The average efficacy of each type of PT, defined as the proportion of safe days where a given therapy was used in which the therapy was efficacious, will be compared. FS-PT will be considered at least as efficacious as CPT if the average efficacy on days where FS-PT was used is no worse than 10% less than the average efficacy on days where CPT was used.

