### Inclusion criteria

Subjects will be eligible to participate in the study if all of the following conditions exist:1) at time of birth, infant is ≥35 weeks gestation (or >2.2 kg if gestational age is not available); 2) infant is ≤14 days old at the time of enrollment; 3) at time of enrollment, infant has an elevated TcB defined as 3 mg/dl below the level recommended for high-risk infants per AAP guideline or higher; 4) parent or guardian has given consent for the infant to participate.

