### Randomization scheme

Enrolled infants with elevated TSB (defined as 3 mg/dl below the level recommended by the AAP to begin PT in high-risk infants) will be randomly assigned to receive FS-PT or CPT. A block randomization procedure with variable block sizes will be used to maximize unpredictability. The randomization assignments of FS-PT or CPT will be printed on sequentially numbered sheets of paper and enclosed in opaque, sealed, sequentially numbered envelopes. The sealed envelopes will be prepared independently by the study statistician based in the USA and transported to Nigeria by the regulatory sponsor. When an enrolled infant’s TSB level is obtained and found to be 3 mg/dl or more below the AAP threshold for high-risk infants the study nurse will request the next envelope. The envelope will be opened and both the envelope number and the treatment assignment will be recorded on the case report form. The laboratory technician responsible for measuring the serum bilirubin level will be unaware of the sequence of treatment allocation of either FS-PT or CPT for each eligible infant and will not be involved in administering PT. The study will not be blinded as it is not physically possible to blind either the participating infants or parents, nor the hospital personnel.

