### Data collection and analysis

Data will be collected on paper case report forms and entered via a web interface into a secure database. The study data will be collected and managed using REDCap (Research Electronic Data Capture) electronic data capture tools hosted at the University of Minnesota’s Academic Health Center. REDCap is a secure, web-based application designed to support data capture for research studies, providing: 1) an intuitive interface for validated data entry; 2) audit trails for tracking data manipulation and export procedures; 3) automated export procedures for seamless data downloads to common statistical packages; and 4) procedures for importing data from external sources.

Demographic data will be summarized and compared between the treatment and control groups using appropriate methods, such as Pearson’s chi-square test for categorical variables and two-sample t-tests for continuous variables. The primary objective is to compare the efficacy of FS-PT and CPT. A 95% exact binomial confidence interval for the true difference in efficacy between the FS-PT treated and CPT control groups will be calculated. FS-PT will be deemed non-inferior to CPT if the calculated confidence interval does not extend more than 10% below the equivalence point.

We plan to conduct three distinct analyses: an intent-to-treat analysis based on the assigned treatment for each enrolled infant, an as-treated analysis based on the actual treatment received on a given day and a per-protocol analysis including only enrolled infants who received the assigned treatment on all of their treatment days.

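### The success rule changes at 72 hours of age, but the primary comparison pools both rules without stratifying by age: a loss of efficiency and interpretability, not of validity

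*Protocol article*

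**What the plan says.** All references are to the protocol article.

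- **Evaluation criteria** sets the first rule: "For infants who are less than 72 hours old in the morning, the treatment will be judged efficacious if the bilirubin level rises more slowly" (the threshold is a rate of 0.2 mg/dl for each hour under treatment). The second rule is: "For infants who are more than 72 hours old, the treatment will be judged efficacious if the bilirubin level falls". Age is judged on the morning of each treatment day.
- The same section combines both rules into one average efficacy per therapy, "defined as the proportion of safe days where a given therapy was used in which the therapy was efficacious, will be compared".
- The two rules cover ages below and above 72 hours; exactly 72 hours belongs to neither. The Background section on the earlier observational study put the same cut at ≤72 and >72 hours.
- **Data collection and analysis** fixes the primary method: "A 95% exact binomial confidence interval for the true difference in efficacy between the FS-PT treated and CPT control groups will be calculated". No age stratum or adjustment is named.
- **Randomization scheme** says "A block randomization procedure with variable block sizes will be used to maximize unpredictability" and names no stratification factor.
- **Inclusion criteria** requires that the "infant is ≤14 days old at the time of enrollment", so both rules will be in use.

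**The concern.** The two rules set different pass marks. Treatment generally runs from 9:00 am to 5:00 pm (Treatment duration), and 8 hours × 0.2 mg/dl per hour = 1.6 mg/dl. An infant of 71 hours whose bilirubin rises by 1.5 mg/dl over the day is a success; one of 73 hours whose bilirubin rises by 0.1 mg/dl is a failure. Age decides which rule applies and is known before treatment starts, so it is the natural stratification variable.

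Two things are at stake.

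- **Precision.** If success rates differ between the age groups, an unstratified interval is wider than it needs to be, in a trial planned at only 80% power.
- **Interpretation.** One pooled difference can hide different results under the two rules. If half the days are under 72 hours and the therapies do not differ there, a pooled deficit of 10 points corresponds to 20 points in the older infants (0.5 × 0 + 0.5 × 20 = 10).

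**Working it through.** **Inputs from the article (Sample size):** 80% efficacy in both groups, margin 10 points, one-sided alpha 0.025, power 80%, equal allocation.

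**Inputs that must be assumed:** the share of days under 72 hours, w, and the gap d between the success rates of the two age groups. The article gives neither; the observational study's 94% (164/175) is not split by age.

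**Step 1: reproduce the plan.** n per group = 2 × 0.80 × 0.20 × (1.960 + 0.842)² / 0.10² = 251.2, so 252, or 504 days in total. Then 504 / 0.90 = 560 and 560 × 1.10 = 616. All match.

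**Step 2: precision of the crude analysis.** The variance per day is 0.16. The standard error of the difference is √(2 × 0.16 / 252) = 0.0356, and the 95% half-width is 1.96 × 0.0356 = 6.98 points. Power = Φ(0.10 / 0.0356 − 1.96) = 80.1%.

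**Step 3: precision when stratified.** With the pooled rate held at 80%, the within-stratum variance is 0.16 − w(1 − w)d². For w = 0.5:

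| Gap d (success under / over 72 h) | Variance | Removed | Half-width | Power at 252 per group | n per group for 80% |
|---|---|---|---|---|---|
| 0 (80% / 80%) | 0.1600 | 0% | 6.98 | 80.1% | 252 |
| 10 points (85% / 75%) | 0.1575 | 1.6% | 6.93 | 80.7% | 248 |
| 20 points (90% / 70%) | 0.1500 | 6.3% | 6.76 | 82.6% | 236 |
| 30 points (95% / 65%) | 0.1375 | 14.1% | 6.47 | 85.7% | 216 |

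With w = 0.3 or 0.7 and a 20-point gap, 5.3% is removed and power is 82.2%. The formula is symmetric in d, so it does not matter which age group does better.

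**Step 4: chance age imbalance.** The between-group difference in the share of days under 72 hours has SD √(2 × 0.5 × 0.5 / 252) = 4.5 points. Multiplied by d, this moves the crude difference by 0.4, 0.9 or 1.3 points (1 SD) for gaps of 10, 20 or 30 points. This is not a second loss on top of step 3. At d = 20 points its variance is 0.0445² × 0.20² = 0.0000794, and the crude variance is 2 × 0.16 / 252 = 0.00127. The ratio is 6.25%, the same variance that stratification removes.

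**Step 5: validity.** In a simulation of 200,000 trials per scenario (252 days per group, w = 0.5, normal-approximation intervals), the crude difference was unbiased with one-sided type I error of 0.025 for every gap from 0 to 30 points. Power, crude against stratified, was 80.2% vs 80.9%, 80.4% vs 82.9% and 80.2% vs 85.7% for gaps of 10, 20 and 30 points.

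**Limit.** These calculations treat days as independent with one day per infant, as Sample size assumes for a typical course.

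**The case against.** The strongest reply is that nothing here is wrong. Infants are randomized, the crude difference is valid, and stratified estimates and subgroup results are often left to an analysis plan, which is not shown. The first part stands in full. The last carries less weight, because the article does name its primary interval and leaves age out of it.

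A second reply also stands: a pass mark that changes with age may offset a different expected course of bilirubin and bring the success rates together. A reader might infer from the two rules that age must strongly predict success. The article does not show this, and with equal rates the loss is zero.

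Third, the only observed rate argues for a small effect. At 94% overall and a 50:50 age split, the gap cannot exceed 12 points (100% against 88%). If both groups succeeded at 94%, power at 252 per group would be Φ(0.10 / √(2 × 0.94 × 0.06 / 252) − 1.96), over 99%, and the lost precision would hardly matter. That figure comes from filtered sunlight alone, and an uneven age split would allow a wider gap, so it tempers the point without removing it.

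A reader might also infer that chance age imbalance biases the result. It does not: it is ordinary sampling variation that the crude interval already covers.

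Finally, stratifying only on age at the start of therapy does not fully match an outcome rule set each morning, since an infant treated over several days can cross 72 hours. That is correct, and the remedy has to address it.

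**Conclusion.** The point holds as one of efficiency and interpretability. The text is clear that the rule changes at 72 hours, that exactly 72 hours is unassigned, and that neither the primary interval nor the described randomization is stratified by age. The size is uncertain and probably small: nothing if the age groups succeed equally often, under 1 power point at a 10-point gap and about 2.5 at 20 points. Only near 30 points is it material, at 5 to 6 power points. All these figures assume half the days under 72 hours and 80% overall success.

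The documents do not support reading this as a bias, an inflated type I error or a wrong sample size.

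One qualification applies where infants contribute several days. Infants leave treatment once bilirubin is no longer elevated (Exit/discontinuation/withdrawal criteria), so the age mix of later days could depend on how fast a therapy works. The as-treated analysis by day is likewise not protected by randomization. The article gives no figures from which to size either effect.

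**What to change.** 1. In Evaluation criteria, define the groups as ≤72 h and >72 h, as in the observational study, so that every infant falls under one rule.
2. Pre-specify the primary risk difference stratified by age group on the first treatment morning, for example a Mantel-Haenszel risk difference or a stratified score interval, with the 10-point margin unchanged.
3. Report success by therapy within each age group.
4. Where infants contribute several days, add a sensitivity analysis stratified by age on the morning of each day, which is how the rule is applied. It belongs as a sensitivity analysis because the age mix of later days can be affected by treatment.

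Age and bilirubin are already needed to apply the two rules, so no new data are required, and the sample size need not change. The cost is a documented amendment. The trial is unblinded and had been randomizing since 29 November 2012 (Trial status), so the amendment should be dated before outcomes are compared between groups.

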### Sample size

The minimum sample size was estimated using the following assumptions: 1) the average efficacy of CPT is 80%; 2) the average efficacy of FS-PT is 80%; 3) there will be the same number of infants assigned to both groups; 4) the delta value is 10% - that is, we want to demonstrate that FS-PT is no more than 10% worse than CPT; and 5) 80% power, one-sided alpha = 0.025.

Under these assumptions, a total of 504 days, or 252 days in each treatment group, will be required. This calculation gives the required number of treatment days that are evaluable for efficacy. Since efficacy will be evaluated only for days in which the treatment was deemed safe, the sample size was increased to account for the possibility that the proportion of safe days might be as low as 90%. Assuming that the safety of both FS-PT and CPT is 90%, a sample size of 560 total days is required. Assuming that a typical course of treatment lasts 1 day, both for FS-PT and CPT, then 560 infants, or 280 infants in each group, will be required. Anticipating up to 10% loss due to rainy days (in the FS-PT group), delisting of infants by parents or guardians, or missing data (in both groups), we will enroll 616 infants, or 308 infants in each group. From our year 1 data in the preceding observational study only 66% of the 826 infants referred for elevated TcB had significant elevated TSB levels, hence 915 infants or more will be enrolled for stage 1 bilirubin estimation until the total requirement of 560 treatment days is reached (Figure 
2).

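### The primary non-inferiority rule is stated two ways, on the observed difference and on the confidence limit, and the two would disagree in about 20% of trials under the plan's own assumptions

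*Protocol article*

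**What the plan says.** The Evaluation criteria section, under Primary outcome, defines average efficacy for each therapy as a proportion: efficacious safe days over all safe days on that therapy. It says the two averages will be compared, and then sets the criterion: "FS-PT will be considered at least as efficacious as CPT if the average efficacy on days where FS-PT was used is no worse than 10" per cent less than the average on CPT days. It mentions no confidence interval, test or error rate.

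The Data collection and analysis section plans a 95% exact confidence interval for the difference in efficacy and gives this rule: "FS-PT will be deemed non-inferior to CPT if the calculated confidence interval does not extend more than 10% below the equivalence point".

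The Sample size section assumes that "the average efficacy of CPT is 80" per cent and "the average efficacy of FS-PT is 80" per cent, that "there will be the same number of infants assigned to both groups", and that "the delta value is 10% - that is, we want to demonstrate that FS-PT is no more than 10% worse than CPT", with "80% power, one-sided alpha = 0.025". It concludes that "a total of 504 days, or 252 days in each treatment group, will be required". The Aims and hypotheses section gives the same 10% margin and takes inferiority as the null hypothesis.

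**The concern.** Read as written, the Evaluation criteria decide the primary claim on the point estimates alone, and the analysis section decides it on a confidence limit. Neither section refers to the other or says which governs.

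A point-estimate rule makes no allowance for sampling error. A therapy lying exactly on the margin would pass about half the time, against the 2.5% the design promises. Any observed deficit between roughly 3 and 10 points would be a success under one section and a failure under the other. The trial is unblinded and, according to the Trial status section, already recruiting, so a single rule should be fixed before results are seen.

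The point concerns the decision threshold only. It does not depend on which days or which analysis set enter the comparison.

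**Working it through.** **Inputs (Sample size section).** Efficacy 0.80 in both groups, margin 0.10, one-sided alpha 0.025 (z = 1.96), power 80% (z = 0.8416), equal allocation, 252 evaluable days per group. Days are treated as independent, in line with the plan's assumption of one treatment day per infant. The 10% is read as absolute percentage points.

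**Step 1: reproduce the plan's figure.**

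n per group = (1.96 + 0.8416)² × 2 × 0.8 × 0.2 / 0.10² = 7.849 × 0.32 / 0.01 = 251.2, rounded up to 252, or 504 in total. The inflations also match: 504 / 0.90 = 560, and 560 × 1.10 = 616. This formula belongs to the confidence-limit rule, so the trial was sized for the rule in the analysis section.

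**Step 2: what each rule demands of the data.**

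Half-width of the 95% interval = 1.96 × √(2 × 0.8 × 0.2 / 252) = 1.96 × 0.0356 = 0.0698.

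- Evaluation criteria: observed difference (FS-PT minus CPT) of -10.0 points or better.
- Analysis section: -10.0 + 7.0, that is, about -3.0 points or better.

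*Illustration.* Take 202/252 efficacious days on CPT (80.2%) and 187/252 on FS-PT (74.2%). The difference is -15/252 = -6.0 points. The standard error is √[(0.802 × 0.198 + 0.742 × 0.258) / 252] = 0.0373, so the Wald 95% interval is -6.0 ± 7.3, or -13.3 to +1.4. The first rule declares success and the second declares failure.

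**Step 3: how often each rule declares success** (252 days per group, CPT 80%, Wald interval):

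| True difference | Evaluation criteria | Analysis section | Gap (points) |
|---|---|---|---|
| 0 | 99.8% | 80.2% | 19.6 |
| -5 points | 91.7% | 26.9% | 64.8 |
| -7 points | 79.5% | 12.2% | 67.3 |
| -10 points | 51.2% | 2.5% | 48.7 |

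The rows for 0 and -10 come from full enumeration of two independent binomial counts. The rows for -5 and -7 come from simulation of 400,000 trials each. A lower confidence limit cannot lie above the estimate, so any trial that passes the interval rule also passes the point rule. The gap is therefore the disagreement rate. A normal approximation at a true difference of 0 gives the same result: 99.7% - 80.1% = 19.6%.

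**Step 4: sensitivity to the interval method and to the number of evaluable days.** At equal efficacy and 252 days per group:

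| Interval | Passes | Rules disagree |
|---|---|---|
| Wald | 80.2% | 19.6% |
| Newcombe | 80.3% | 19.5% |
| Score | 79.9% | 19.8% |
| Exact unconditional | 78.9% | 20.8% |

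With more evaluable days the disagreement at equal efficacy shrinks, to about 16% at 280 per group and 12.5% at 308. The error rate at the margin does not: the point rule passes 51.9% at 280 and 48.9% at 308 when FS-PT is truly 10 points worse.

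**The case against.** The best defence is that the sentence in the Evaluation criteria states the margin and was never meant as a test. It does not use the word observed. The Sample size section uses average efficacy for an assumed true value and describes delta in similar terms, where it plainly means the margin. The Secondary outcome section puts its 5% margin in the same form. The analysis section alone names an interval and a verdict, and the Aims and Sample size sections agree with it. A condensed article may reasonably state the margin in one place and the inference in another.

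It can also be said that the 20% is generic. It is close to one minus the planned power, and any non-inferiority trial with 80% power would show a similar gap between a point rule and an interval rule.

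Much of this stands. The other sections show which rule was intended, which makes this a wording repair and leaves the design intact. The figures do measure the gap between the rules; they do not predict which rule the investigators would apply.

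The conflict remains, however. The sentence sets a condition for success, and it applies that condition to a quantity the same section has just defined as a proportion of treatment days. The margin as such is already given under Aims and hypotheses. As for the smaller disagreement at 280 or 308 days, 252 is the evaluable count the plan expects after its allowances for unsafe days and losses.

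**Conclusion.** The concern holds. The article prints two success rules for its primary endpoint, and only the confidence-limit rule has the stated alpha and power. Under the plan's own assumptions (252 evaluable days per group, 80% efficacy in both, independent days) the rules disagree in 19.6% of trials, or 19.5% to 20.8% across four interval methods. The disagreement runs one way: the Evaluation criteria pass FS-PT where the analysis section does not. At a true deficit of 10 points the point rule has a one-sided error rate of about 51%, against 2.5%. The risk is thus an unsupported claim of non-inferiority if the Evaluation criteria were taken as the governing text. It should be corrected, but it does not undermine the sample size or the planned analysis.

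**What to change.** Replace the last sentence of the Evaluation criteria section with the rule already in the analysis section, for example:

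*FS-PT will be declared non-inferior to CPT if the lower limit of the two-sided 95% confidence interval for the difference in efficacy (FS-PT minus CPT) is above -10 percentage points.*

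Delete the criterion based on the averages alone, so that one rule decides the trial.

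The cost is one sentence of wording, to be documented before outcome data are reviewed. The margin, sample size, data collection and analysis stay as they are. The bar becomes stricter than the one printed in the Evaluation criteria, but it is the one the trial was sized for.
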